## Abstract

**Background:**

The main hypothesis of this study is that patients having regular conventional haemodialysis (HD) will have a smaller decline in cardiac systolic function by using cooler dialysate. Cooler dialysate may also be beneficial for brain function.

**Methods/Design:**

The trial is a multicentre, prospective, randomised, un-blinded, controlled trial. Patients will be randomised 1:1 to use a dialysate temperature of 37°C for 12 months or an individualised cooled dialysate. The latter will be set at 0.5°C less than the patient’s own temperature, determined from the mean of 6 prior treatment sessions with a tympanic thermometer, up to a maximum of 36°C. Protocol adherence will be regularly checked. Inclusion criteria are incident adult HD patients within 180 days of commencing in-centre treatment 3 times per week with capacity to consent for the trial and without contra-indications for magnetic resonance imaging. Exclusion criteria include not meeting inclusion criteria, inability to tolerate magnetic resonance imaging and New York Heart Association Grade IV heart failure. During the study period, resting cardiac and cerebral magnetic resonance imaging will be performed at baseline and 12 months on an inter-dialytic day. Cardiovascular performance during HD will also be assessed by continuous cardiac output monitors, intra-dialytic echocardiography and biomarkers at baseline and 12 months. The primary outcome measure is a 5% between-group difference in left ventricular ejection fraction measured by cardiac magnetic resonance imaging at 12 months compared to baseline. Analysis will be by intention-to-treat. Secondary outcome measures will include changes in cerebral microstructure and changes in cardiovascular performance during HD. A total of 73 patients have been recruited into the trial from four UK centres. The trial is funded by a Research for Patient Benefit Grant from the National Institute of Healthcare Research. AO is funded by a British Heart Foundation Clinical Research Training Fellowship Grant. The funders had no role in the design of the study.

**Discussion:**

This investigator-initiated study has been designed to provide evidence to help nephrologists determine the optimal dialysate temperature for preserving cardiac and cerebral function in HD patients.

**Trial registration:**

ISRCTN00206012 and UKCRN ID 7422

## Background

It is well recognised that HD patients suffer excess cardiac morbidity and mortality and this is mainly due to cardiac failure and sudden cardiac death. Interventions of proven benefit in the non-HD population have thus far been ineffective in HD patients and there is a need for a novel approach.

### Haemodialysis induced myocardial ischaemia

In the setting of coronary artery disease without kidney disease, transient myocardial ischaemia may lead to left ventricular dysfunction that can persist for several hours after the return of normal perfusion, but is eventually followed by functional recovery. This reversible post-ischaemic dysfunction is known as myocardial stunning. Repetitive episodes of stunning are cumulative eventually leading to hibernation then irreversible contractile dysfunction [1]. The ability of HD to induce myocardial ischaemia had been long suspected with reports of silent, reversible ischaemic ECG changes during HD older than twenty years. Other studies showed elevated cardiac troponins were common and up to 30% of HD treatments were complicated by significant intra-dialytic hypotension [2]. These data suggested HD might induce myocardial ischaemia but were unable to prove this or elucidate the pathophysiology. Subsequent proof-of-concept studies by our group and others in subjects with normal coronary arteries have demonstrated that HD is characterised by a 30% reduction in regional myocardial blood flow by H_2_^15^O positron emission tomography [3]. The decreased myocardial blood flow localises to the same segments as regional wall motion abnormalities (RWMAs) using simultaneous 2D-echocardiography at peak-stress, 15 minutes before the end of a HD treatment compared to pre-HD [3]. This supported use of these stress-RWMAs as a practical surrogate for myocardial ischaemia. These changes in the absence of coronary artery disease can be explained by decreased coronary flow reserve which is well described in dialysis populations [4] and is in turn promoted by a high prevalence of autonomic dysfunction, endothelial dysfunction, left ventricular hypertrophy and arterial stiffness. These factors may underlie the reduced sensitivity and specificity of ischaemia stress testing in HD patients [5]. The HD procedure involves a rise in core temperature, extracorporeal circuit, fluid removal and exposure to a dialysis membrane which combine to form a haemodynamic stress provoking demand ischaemia [6]. Our natural history study of 70 prevalent HD patients showed that compared to pre-HD echocardiography, new RWMAs developed at peak-stress in 45 participants and this associated with 30% mortality and 13% reduction in mean left ventricular ejection fraction by 1 year [7,8]. RWMAs persisted at follow-up in the 36/45 survivors of the subgroup. In the cohort who had no abnormal segments at the start of the study, new segmental RWMAs had also developed. Multivariable analysis showed the significant determinants of these stress-RWMAs were age, ultrafiltration volume, intra-dialytic hypotension and serum troponin-T concentration and this displaced all other variables including diabetes status and history of ischaemic heart disease [7]. In short, the RWMAs characterise those who suffer ischaemia due to the haemodynamic stress of HD. Regardless of the balance of micro- and macrovascular disease in the pathophysiology, reducing these RWMAs represents a valid target and may lead to detectable amelioration of global ventricular function.

### Rationale for cooling

Extending the frequency and length of dialysis to reduce ultrafiltration volumes and rates might be one approach to improve cardiac outcomes but the access to and acceptability of this strategy might be limited and unfeasible in some healthcare systems [9]. Novel approaches to reduce RWMAs within the constraints of a standard 4 hour treatment and without the need for invasive tests are needed to retard the development of irreversible cardiac dysfunction and reduced survival. Our pilot studies have demonstrated that cooling the dialysate used during HD reduces the number of episodes of intra-dialytic hypotension and the proportion of patients who develop RWMAs [10-12]. The mechanisms by which lower dialysate temperature may improve haemodynamic instability include reducing heat transfer from the dialysate which contributes to dilation of thermoregulatory blood vessels [13,14]. Cooling the dialysate is not a new intervention [15]. However, prior studies have used prevalent patients, not been randomised or lasted less than one month focussing on short-term benefits of preventing intra-dialytic hypotension. They have also lacked statistical power to detect outcomes validated to predict development of heart failure, mortality and hospitalisation. This study is novel in that the population is incident, the intervention is applied for one year and it is designed to detect long-term changes of validated surrogate outcomes. There are many strategies employed in cooling the dialysate and we previously conducted a systematic review [16]. These include:

 1. Fixed temperature reduction

 2. Biofeedback systems which vary dialysate temperature to deliver either;

 a. no overall change in the patient’s blood temperature (isothermic dialysis)

 b. lowering of the patient’s blood temperature (hypothermic dialysis)

 3. Sequential fixed temperature reduction to a minimum of 35°C or the minimum tolerated above 35°C.

We elected for cooling the dialysate to 0.5°C less than the patient’s temperature (determined with a tympanic thermometer) as a pilot study of 11 patients showed this might achieve the same benefit without the symptoms of cold intolerance which may have been a factor in preventing more widespread use of this strategy [12]. Biofeedback dialysis is a potentially attractive option but has the major disadvantage of requiring specialised dialysis machines which are not universally available. Previous pilot data in short-term studies demonstrated the potential benefit in terms of reduced RWMAs of cooler dialysate which is available on all dialysis machines and can be implemented with minimal or no financial impact.

### Plausibility of HD induced cerebral ischemia

It is increasingly recognised that HD patients exhibit higher levels of functional and cognitive deficits. Dementia is highly prevalent in the HD population with a reported 7-fold relative risk of developing multi-infarct dementia within a year of commencing dialysis compared to age-matched controls; delirium and depression were also found to be common in this population when followed for a period of 4 years [17,18]. Furthermore, even HD patients with normal dementia scores develop neurocognitive dysfunction affecting retention of complex verbal information, memory, executive function, language and mental processing speed [19,20]. Few studies have linked cognitive impairment with findings on brain imaging. Cerebral atrophy is a common finding in HD patients [18,21]. However, the predominant morphological abnormalities reported are white matter hyperintensities termed leukoaraiosis. These areas of high signal on T2-weighted MRI represent white matter ischemia characterised by neuronal loss and demyelination. Although leukoaraiosis develops with aging as a reflection of the burden of cardiovascular disease, many studies report a greater volume of leukoaraiosis in dialysis patients compared with age-matched controls [22,23]. A recent meta-analysis showed leukoaraiosis was associated with a higher risk of stroke, dementia and death in the general population [24]. Adequate perfusion of brain white matter depends on blood pressure and the brain’s autoregulatory capacity [25]. HD can induce haemodynamic and circulatory stress and HD patients have impaired autonomic function and autoregulatory capacity rendering them vulnerable to those haemodynamic changes [26]. Hence the HD process might play an important role in the pathogenesis of brain injury in HD patients.

### Hypothesis

We propose a study to determine whether cooling the dialysate retards the longer term development of cardiac systolic dysfunction. This study will also examine whether cooling the dialysate will have an abrogating effect on cerebral ischaemia and a wide range of functional measures including haemodynamics, microvascular function and validated measures of cognitive impairment. This work has the potential to reveal a refined yet pragmatic intervention to combat excess cardiovascular disease in HD patients.

## Methods/Design

Ethical approval for trial has been obtained from Nottingham Ethics Committee for all participating centres prior to study initiation and patient enrolment. The study will be performed in accordance with the Research Governance Framework, International Conference on Harmonisation Good Clinical Practice Guideline and the 2000 Scotland Revision of the Declaration of Helsinki. All participants are to provide written informed consent before any trial related procedure can occur.

### Participants

Patients must fulfil the following eligibility criteria to be considered for the study enrolment or participation:

Inclusion criteria:

 1. Patients having in-centre HD at least 3 times per week.

 2. Willing and able to provide consent.

 3. Male and female, age ≥ 16 years old.

Exclusion criteria:

 1. Exposure to haemodialysis for >180 days

 2. Contraindications for using MRI (eg. pacemakers and metal implants, pregnancy or lactating)

 3. Inability to tolerate MRI due to claustrophobia

 4. New York Heart Association grade IV heart failure

 5. Mental incapacity to consent

### Study design

The schedule of events is summarized in Figure 1. The trial is a multicentre, prospective, randomised, un-blinded, controlled trial. Patients will be recruited from 4 research sites and randomised 1:1 to the control group or intervention group. Randomisation will be in a single block by sealed envelopes generated by an independent statistician. The control group will use a dialysate temperature of 37°C for 12 months. The intervention group will have an individualised cooled dialysate temperature for 12 months. This will be set at 0.5°C less than the patient’s own temperature, determined from the mean of 6 prior treatment sessions with a tympanic thermometer, up to a maximum of 36°C, ensuring a minimum temperature separation of 1°C between groups. Adherence to the allocated dialysate temperature will be regularly checked and recorded by nursing staff at each research site enabling distinction between the prescribed and delivered dialysate temperatures. Analysis will be by intention-to-treat regardless of any crossover between delivered temperatures.

**Figure 1 F1:**
[figure not shown]
Trial design.

### Blinding

This is an un-blinded study. Therefore, after randomisation, the investigators, HD unit staff and patient will be aware of group allocation. This is necessary to ensure adherence to the study protocol. There will be blinding of treatment allocation for analysis of cardiac images for the primary outcome.

### Concurrent treatments

Patients in each trial arm will undergo standard management, as per local HD unit protocols with the exception of dialysate temperature.

### Cardiac and cerebral magnetic resonance imaging

Contrast-free cardiac and cerebral MRI will be performed at baseline and 12 months when the patient has been established on HD with a stable dry weight unchanged for at least 4 weeks. Studies will occur on non-dialysis days at two centres using a 1.5 T MRI scanner (GE Signa HDxt 1.5 T, GE Healthcare, Milwaukee,US). Acquisition will include serial contiguous short-axis cines piloted from vertical or horizontal long axis of the left ventricle using ECG-gated steady-state in free precession sequences in accordance with validated methodologies [27]. Analysis will be performed with the anonymised images off-line by planimetry using commercially available software for assessment of ventricular volumes and mass. Brain MRI will examine the integrity and microstructure of white matter using diffusion tensor imaging. The anonymised images will be analysed off-line for diffusivity and anisotropy corrected for brain volume.

### Cognitive assessment

Cognitive assessment will be performed on the same day as the MRI scans at baseline and 12 months. The Montreal Cognitive Assessment is a validated tool for the detection of mild cognitive impairment with higher sensitivity and specificity than the Folstein Mini-Mental State Examination for the detection of mild cognitive impairment [28]. Trail Making Tests A and B will be used to examine attention and mental flexibility.

### Assessing cardiovascular performance during HD

Detailed characterisation of cardiovascular performance will be assessed during HD at baseline and 12 months. This occurs during the patient’s usual HD session in their own centre using the same portable data collecting instruments across all centres. 2-dimensional echocardiography will be performed using commercially available equipment (1.5-4Mhz probe, Vivid-I, GE Healthcare) by one of two trained technicians in the left lateral position. Sector width, frequency and depth will be adjusted to produce optimal border definition and a frame-rate of 50–80 per second. Standard apical 2 and 4-chamber image loops will be recorded pre-dialysis (rest) and 15 minutes before the end of dialysis (stress). Image loops will be anonymised and analysed off-line in random order for regional deformation using dedicated software (EchoPac, GE Vingmed). Continuous non-invasive cardiac output monitoring will be recorded using a thoracic bioreactance monitor (NICOM™, Cheetah Medical). This uses phase changes in alternating electrical current to derive cardiac output. This endows a greater precision and signal-to-noise ratio than impedance cardiography. The monitor is validated in both healthy and co-morbid adults [29]. The Finometer™ (TNO Instruments) utilises a finger-cuff to detect beat-to-beat changes in digital arterial pressure and calibrates this against oscillometric brachial artery pressure. The Finometer™ is validated in critical care and HD settings [30].

### Arterial stiffness and body composition

Arterial stiffness measured by pulse wave velocity is independently associated with increased risk of cardiovascular disease in HD patients [31]. Carotid-Femoral pulsewave velocity will be measured by a volume displacement technique [32]. Pre-HD body composition and hydration status will be estimated by segmental multi-frequency bioimpedance [33].

### Primary study outcome

Change in resting LVEF by cardiac magnetic resonance (CMR) at 12 months compared to baseline between the intervention and control group.

### Secondary study outcomes

 · Left ventricular mass by CMR

 · Regional myocardial deformation by speckle-tracking echocardiography and CMR tagging.

 · A range of haemodynamic variables, including cardiac output, pulse rate, heart rate and frequency of intra-dialytic hypotension

 · Change in body composition by bioimpedance

 · Change in cerebral diffusion tensor MRI

 · Change in cognitive assessment scores

 · Change in soluble cardiac biomarkers

### Rationale for primary outcome

We selected LVEF measured by CMR as the primary outcome because previous observational study showed mean reduction in LVEF by echocardiography of 13% over 12 months in patients who displayed RWMAs at baseline. RWMAs were abrogated in the short-term by a dialysate cooling strategy in a separate cohort [10,12]. We also selected LVEF as an objective measure which is predictive of mortality and hospitalisations [34]. A change in LVEF greater than 5% has been shown to be an important cut-off approaching the minimum clinically important difference [35,36]. CMR is the gold-standard for measurement of left ventricular mass and volumes, allowing determination of the primary outcome to a much higher precision compared to alternative methods such as echocardiography. This markedly reduces the sample size required to detect between-group differences in an intervention trial, permitting lower costs and faster reporting of final results [37,38]. Sample estimation is from a recent reference range study which used the same CMR acquisition and analytic techniques planned for this study [27] and were performed by a medical statistician using commercially available software (Nquery Advisor v6).

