### Sample size estimation

The primary aim in this study is to detect a 5% difference in LVEF as measured by CMR between the control and intervention group after 12 months. Using a two sample t test and assuming a mean LVEF of 67% in the control arm and equal Standard Deviation in each group of 6% [27], a study of 64 participants (32 per group) would permit the detection of a 5% difference in LVEF from baseline to 12 months between the intervention and control groups, with 90% power at 5%, 2-sided significance level. Allowing for study attrition and death of 10%, we aim to recruit 72 participants to achieve an evaluable sample of 64 participants.

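### The primary LVEF comparison is fixed as unadjusted, although the protocol treats baseline stress-induced RWMAs as the marker of LVEF loss and already records the echocardiography that would show them

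*Protocol article*

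**What the plan says.** All references are to the protocol article.

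- **Primary outcome** (Primary study outcome): "Change in resting LVEF by cardiac magnetic resonance (CMR) at 12 months compared to baseline between the intervention and control group".
- **Reason for choosing it** (Rationale for primary outcome): the first reason is that a "previous observational study showed mean reduction in LVEF by echocardiography of 13% over 12 months in patients who displayed RWMAs at baseline". The section adds that cooling suppressed RWMAs in the short term in another cohort, and that LVEF predicts death and hospitalisation.
- **Source cohort** (Haemodialysis induced myocardial ischaemia): among 70 prevalent patients, "new RWMAs developed at peak-stress in 45 participants". The same section says that patients free of abnormal segments at the start later developed them too.
- **Eligibility** (Participants): the first inclusion criterion is "Patients having in-centre HD at least 3 times per week". Neither list mentions RWMAs.
- **Randomisation** (Study design): a single block, with no stratification factor stated.
- **Baseline measurement** (Assessing cardiovascular performance during HD): at baseline and 12 months, "Standard apical 2 and 4-chamber image loops will be recorded pre-dialysis (rest) and 15 minutes before the end of dialysis (stress").
- **Sample size** (Sample size estimation): the target is worded as "The primary aim in this study is to detect a 5% difference in LVEF as measured by CMR between the control and intervention group". The calculation is then made by "assuming a mean LVEF of 67% in the control arm and equal Standard Deviation in each group of 6"%, with 32 per group for 90% power.
- **Analysis** (Statistical methods): a t test or Mann-Whitney test between arms at set times, plus a repeated-measures analysis whose terms are not given. RWMAs enter through a Poisson regression that compares their frequency between arms.

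**The concern.** The protocol's only evidence that LVEF falls over a year comes from patients with stress-induced RWMAs, and its background section presents RWMAs as the sign of who is harmed by dialysis. If that is right, baseline RWMA status should predict the 12-month change in LVEF. A two-group test that ignores a strong predictor leaves its variance in the error term. In a trial with 32 evaluable patients per arm, that can matter.

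The SD of 6 comes from a reference range study and is used as the SD in each arm. The documents do not say whether it allows for a mixture of patients who decline and patients who do not. If it does not, the achieved power is below the planned 90%, although the information needed to recover most of the loss is already being collected.

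**Working it through.** **Inputs from the documents.** Difference 5 points, SD 6, two-sided 5%, 32 per arm; RWMA prevalence p = 45/70 = 0.643; LVEF decline 13% in RWMA-positive patients. The documents do not say whether 13% is in points or relative, so both are shown: D = 13, or D = 0.13 × 67 = 8.7.

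**Assumptions, not in the documents.** The 45/70 share carries over from prevalent to incident patients. SD 6 is the SD of LVEF change within each RWMA stratum. The echocardiographic decline applies to CMR.

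**1. The plan's own figure.** A two-sample t test (noncentral t) with difference 5 and SD 6 needs 31.25, so 32 per arm. Power at 32 is 90.7%. 64/0.9 = 71.1, so 72 recruited. The plan's figures reproduce, and the 13% is not an input to them.

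**2. Is there room for a 5-point whole-arm effect?** If only RWMA-positive patients decline, the most that cooling could prevent is p × D = 0.643 × 13 = 8.4 points, or 0.643 × 8.7 = 5.6 points. Both exceed 5.

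**3. Unadjusted power with decline and effect only in RWMA-positive patients.**
- Effect in them that gives 5 overall: 5/0.643 = 7.8 points.
- p(1 − p) = 0.643 × 0.357 = 0.2296.
- Control-arm variance from the mixture: 0.2296 × 13² = 38.8 (or 0.2296 × 8.71² = 17.4).
- The gap between strata in the cooled arm shrinks to 13 − 7.8 = 5.2 (or 8.7 − 7.8 = 0.9), so its mixture variance is 6.3 (or 0.2).
- Averaged SD: √(36 + (38.8 + 6.3)/2) = 7.65 (or √(36 + (17.4 + 0.2)/2) = 6.69).
- Power at 32 per arm: **73%** (or **84%**).

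**4. The same scenario with RWMA status as a main-effect covariate.** A common RWMA term removes the average gap. Half of the 7.8-point effect difference remains in each arm: √(36 + 0.2296 × 3.89²) = 6.28. Power is about **88%** on either reading.

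**5. RWMA-negative patients decline half as much.** The gap becomes 6.5 (or 4.36). If cooling gives the same 5 points in both strata, the gap is equal in both arms. SD is √(36 + 0.2296 × 6.5²) = 6.76 (or √(36 + 0.2296 × 4.36²) = 6.35), and unadjusted power is **83%** (or **87%**). A covariate would bring the SD back to 6.

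**6. SD 6 already includes the RWMA spread.** Unadjusted power is then 90.7% as planned, and adjustment adds to it. A control-arm gap of 13 points could not fit inside it, because 38.8 exceeds 6² = 36; a gap of 8.7 could, because 17.4 does not.

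**7. Precision of a treatment-by-RWMA estimate.** Of 64 evaluable patients, about 41 would be RWMA-positive and 23 negative. With equal arms in each stratum, SE = √(36 × (4/41.1 + 4/22.9)) = 3.1, so the 95% CI is about ±6 points.

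**The case against.** **The design is not in error.** Randomisation makes the unadjusted comparison valid, and enrolling unselected incident patients is a reasonable choice for a trial that calls itself pragmatic. Both points stand, and nothing here asks for selection on RWMAs.

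**A reader might infer that the effect is diluted**, because about a third of patients may have no decline to prevent. The documents do not support this. The 5% is a whole-arm target argued from clinical importance: "A change in LVEF greater than 5% has been shown to be an important cut-off approaching the minimum clinically important difference". Step 2 leaves room for it, though narrowly on the relative reading. Patients initially free of RWMAs also went on to develop them, and no LVEF change is reported for that group, so zero decline in them is an assumption.

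**A reader might also put unadjusted power at 62% or 77%.** Those figures keep the full 13- or 8.7-point gap in both arms. That contradicts a cooling effect confined to RWMA-positive patients, which must shrink the gap in the cooled arm.

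**RWMAs are used in the analysis.** They are, as an outcome. What is absent is their use in the LVEF comparison.

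**Covariates belong in an analysis plan that is not shown.** This has weight: such a plan may exist, and the repeated-measures terms are not given. But the Statistical methods section is not silent. It names an unadjusted two-group test for the primary endpoint, and the point is an improvement on that stated choice.

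**Conclusion.** The point holds as a matter of precision, not of validity. By the protocol's own account, baseline stress-RWMA status is the most plausible predictor of LVEF change. It can be derived from planned baseline echocardiography, and the stated primary test ignores it.

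The size is conditional. With decline and benefit confined to RWMA-positive patients and SD 6 within strata, adjustment raises power by about 15 percentage points (73% to 88%) if 13% means points, and by about 4 (84% to 88%) if it is relative. With half the decline in RWMA-negative patients, unadjusted power of 83% to 87% is already near plan. If SD 6 is the total spread, nothing is lost against the plan. The documents do not give RWMA prevalence in incident patients, the LVEF change in RWMA-negative patients, the SD of change or the scale of the 13%, so no single figure can be fixed. The change is worth making because it costs little.

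**What to change.** In Statistical methods, replace the t test or Mann-Whitney choice for the primary endpoint with one pre-specified model: a linear regression of 12-month change in LVEF on randomised arm and baseline stress-RWMA status, with the arm coefficient and its 95% CI as the primary result. Define RWMA status from the baseline rest and peak-stress loops, before outcome data are analysed by arm. Keep patients with a missing baseline echocardiogram in the analysis, by a rule set in advance that uses baseline information only and is the same in both arms.

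The cost is one degree of freedom and that missing-value rule; the echocardiography is already planned. Recruitment is reported complete, so the analysis is the part that can still be changed.

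A treatment-by-RWMA estimate is optional. At about ±6 points it is wider than the 5-point effect sought, so it should be reported with its CI and labelled supportive only. Eligibility needs no change.
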